### Self-Care Self-Efficacy Framework

A self-care self-efficacy (SCSE) framework emerges as a valuable theoretical model for developing a measure of OAC-specific SE by being rooted in the middle-range theory of self-care for chronic illness [11,12] and Bandura’s [13] social cognitive theory. In this framework, the SCSE is the patient’s confidence in self-care maintenance (actions to maintain physiological stability), monitoring (efforts to detect signs and symptoms), and management (actions to address functional health behaviors) [14].

The SCSE framework can help researchers and clinicians effectively address OAC-specific challenges related to self-care behaviors in patients undergoing OAC treatment. This approach facilitates the creation of a theory-grounded SE scale that can discern and evaluate complex situations in the context of OAC. These situations involve the behaviors patients need to adhere to maintain physical and mental stability over time (maintenance), monitor signs and symptoms, and implement appropriate actions for symptom management (management) [11,12]. Consequently, the SE within this framework will assess a patient’s confidence in performing these demanding self-care tasks associated with OAC, encompassing decision-making processes, cognitive functioning, and overall health literacy [11,12].

For example, some behaviors investigated within the 3 domains of self-care may reflect how well patients respond to tailored education and preparedness. Other behaviors might address shared challenges in maintaining a healthy status, monitoring changes in the body and mental well-being while on OAC treatment, and making informed decisions in response to unexpected changes. As the project expands, these behaviors could be further tested and integrated into OAC-specific self-care measures. Therefore, developing the Self-Care Self-Efficacy Index in Oral Anticoagulation Therapy Management (SCSE-OAC) aims to offer a comprehensive and nuanced understanding of patients’ SE in managing their OAC treatment effectively by using and incorporating the SCSE framework.

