The patients’ eligibility criteria will be adult outpatients (18 years of age or older) with ongoing treatment with OAC at the time of the investigation, with a primary clinical indication for long-term OAC for NVAF, treated for at least 3 months, and who are willing to participate in the study. Instead, patients with cognitive decline (ie, Six Item Screener Test with lower than 4 points) will be excluded. Likewise, a convenience sample of 10 voluntary professionals from all relevant disciplines (ie, physician, nurse, and pharmacist) with documented clinical experiences in OAC for at least 1 year will be involved. Sociodemographic and professional variables will be considered to provide a sample description. Finally, an open-ended question will be included to assess the comprehensive and comprehensibility criteria. More specifically, participants will be asked to evaluate whether the items together comprehensively cover the construct of interest and if the population of interest clearly understands the items and response options to evaluate the face validity. The responses will be systematically analyzed, coded, and compared through a qualitative content analysis approach. Data collection will be done through an e-survey.

Following the achievement of content and face validity, 3 forms of validity will be tested—structural, cross-cultural, and criterion validity. As per the structural validity, we will assess the dimensionality of the construct to be measured (ie, SCSE) by factor analysis. However, no clear hypotheses about the underlying dimensions of the construct in the OAC population are available. Therefore, a 2-fold cross-validation will be performed for each language group, using explorative factor analysis (EFA) to explore relationships between observed variables and underlying factors and identify the most plausible psychometric structure and confirmatory factor analysis (CFA) to confirm the most plausible structure derived from EFA. More specifically, the overall sample for each language group will be randomly resampled to generate a subsample A for performing EFA (roughly 50% of the original sample) and subsample B for performing a CFA using the most plausible psychometric structure derived from EFA (using the second 50% of the original sample).

### Sample Size for Phase 2

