In the field of factor analysis, the sample size estimation for allowing researchers to perform factor analysis properly is based on a rule of thumb supported by the Monte Carlo simulation study of enrolling 10 patients per item and per language group [25]. As a result, the final required sample size will be based on the version of the SCSE-OAM derived from the content validity phase because it depends on the number of items encompassed in the scale. Considering previous similar research in patients with heart failure, 10 items were developed for measuring SCSE for adults with heart failure. We hypothesized a similar number of items. In this case, 100 patients per language group will be necessary for EFA and subsequently for CFA.

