Clinical variables (ie, time in therapeutic range and absence of hemorrhagic and thromboembolic complications) will be used to estimate the cutoff points of adequate versus inadequate patients’ SCSE and assess criterion validity, which is the degree to which the score of the SCSE-OAM is an adequate reflection of good anticoagulation control. Sensitivity and specificity analyses will be performed under the receiver operator characteristic curve by using time in the therapeutic range and absence of hemorrhagic and thromboembolic complications as dichotomic outcomes (if the distribution of the outcomes will allow researchers to perform this analysis).

### Phase 3

The third phase of this research protocol focuses on evaluating the reliability and internal consistency of the SCSE-OAM over time. This phase, which is anticipated to end by December 2025, aims to ensure the stability of the developed scale. Two main criteria will be used for this assessment—internal consistency and reliability.

For internal consistency, the degree of interrelatedness among the items of the SCSE-OAM will be evaluated using Cronbach α. This index will be calculated for each unidimensional subscale, as well as for the overall scale. A Cronbach α value equal to or greater than 0.70 will be considered acceptable, indicating a strong internal consistency.

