## Discussion

### Principal Findings

This research protocol addresses a critical gap in OAC management by focusing on developing and validating SCSE for OAC treatment (SCSE-OAC). OAC is an internationally recommended treatment for patients with NVAF and plays a crucial role in preventing venous thromboembolism and stroke while requiring the adjustment of lifestyle to the chronic treatment that requires adherence [2,9,28]. However, low levels of adherence and persistence to OAC have been observed by previous research [29], leading to potentially preventable thromboembolic and hemorrhagic complications [30]. Understanding the determinants underlying patients’ adherence to OAC, particularly their SE, is of paramount importance to designing personalized patient-centered educational interventions. The SCSE-OAC, being a specific and theory-grounded tool, will aid in capturing patients’ confidence in performing self-care behaviors and provide insights into the challenges they face in OAC management. Consequently, the study’s findings will contribute significantly to enhancing treatment adherence, safety, and overall health outcomes for patients with NVAF.

The study aims to provide a comprehensive SCSE-OAC for English- and Italian-speaking populations through a multiphase and mixed methods research design. In the conceptualization phase, a systematic literature review will help identify challenges and issues in OAC self-care management. Subsequently, qualitative and quantitative methodologies involving patients and experts will refine the initial items’ pool. The validation phase will focus on establishing the internal validity of the SCSE-OAC using Cronbach α, ensuring the tool’s reliability and consistency. Additionally, a test-retest reliability study will assess the stability of the SCSE-OAC over time. Overall, the study is expected to yield a robust and culturally adapted SCSE-OAC that can be applied to evaluate patients’ SE levels in OAC management for each native-speaking group involved in the research.

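### Overall Cronbach alpha of at least 0.70 is read as strong internal consistency whether or not the scale proves unidimensional

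*Protocol article*

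**What the plan says.** All references are to the protocol article.

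- **Methods, Phase 3: coefficient.** Alpha is the only internal-consistency index named: "the degree of interrelatedness among the items of the SCSE-OAM will be evaluated using Cronbach α".
- **Methods, Phase 3: scope.** "This index will be calculated for each unidimensional subscale, as well as for the overall scale".
- **Methods, Phase 3: threshold and reading.** "A Cronbach α value equal to or greater than 0.70 will be considered acceptable, indicating a strong internal consistency".
- **Methods, Phase 2: Validation.** The structure is left open, because "no clear hypotheses about the underlying dimensions of the construct in the OAC population are available". Exploratory factor analysis (EFA) is run in one random half of each language group and CFA in the other.
- **Introduction, Self-Care Self-Efficacy Framework.** The construct is built on maintenance, monitoring and management. The text speaks of "some behaviors investigated within the 3 domains of self-care".
- **Methods, Sample Size for Phase 2.** The expected length comes from a heart-failure scale: "10 items were developed for measuring SCSE for adults with heart failure. We hypothesized a similar number of items".
- **Methods, Data Analysis.** Items loading above 0.40 are kept. The EFA-derived model is tested by CFA with the usual fit indices and then by multi-group CFA across languages. Neither a second-order model nor an omega coefficient is mentioned.
- **Methods, end of Data Analysis.** ROC analysis is to find cutoffs for adequate and inadequate self-efficacy. The scale's score is referred to in the singular, without a scoring rule.
- **Discussion, Principal Findings.** The validation phase is described as "establishing the internal validity of the SCSE-OAC using Cronbach" alpha.

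**The concern.** By naming unidimensional subscales, the plan accepts that the whole scale may not be unidimensional. It then applies the same threshold and the same favourable label to the whole. Alpha rises with the number of items and with the average inter-item correlation. High correlations within factors can lift that average even when the factors are weakly related, so alpha does not show that a sum over factors reflects one thing.

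What is at stake is the reading of a total score, if one is formed. A report could call the internal consistency of the total strong when most of its variance is not shared across domains. A single ROC cutoff on such a total could let high confidence in one domain mask low confidence in another.

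Two wording problems need no assumptions. The lowest passing value is called both acceptable and strong. The Discussion assigns alpha to establishing internal validity in the validation phase, whereas Methods assigns it to internal consistency in Phase 3 and assesses validity by other means.

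**Working it through.** The 0.70 threshold is a chosen criterion with nothing behind it to reproduce. The check is what a scale can look like when it passes.

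**Inputs**
- From the article: about 10 items (k = 10); threshold 0.70; three domains, used here as a 4/3/3 layout.
- Assumed, because the article gives neither: equal standardized loading L and equal factor correlation φ.

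**Formulas**
- Items in the same factor correlate L²; items in different factors correlate φL². S is the sum of all entries of the correlation matrix.
- Alpha = k/(k−1) × (1 − k/S).
- Omega-hierarchical (ω_h), the share of total-score variance due to a common factor, = φL²k²/S. Each item's loading on the common factor is L√φ.
- With k = 10, alpha ≥ 0.70 means 1 − 10/S ≥ 0.63, so S ≥ 10/0.37 = 27.03.

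**4/3/3 layout.** Of the 90 off-diagonal entries, 12 + 6 + 6 = 24 are within factors and 66 between.
- L = 0.7, φ = 0.2: S = 10 + 24(0.49) + 66(0.098) = 28.23. Alpha = (10/9)(1 − 10/28.23) = 0.72. ω_h = 9.8/28.23 = 0.35.
- L = 0.7, φ = 0.3: S = 10 + 11.76 + 66(0.147) = 31.46. Alpha = 0.76. ω_h = 14.7/31.46 = 0.47.
- L = 0.7, φ = 0.5: S = 10 + 11.76 + 66(0.245) = 37.93. Alpha = 0.82. ω_h = 24.5/37.93 = 0.65.

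**Limits of the window at L = 0.7**
- Alpha reaches 0.70 when 21.76 + 32.34φ = 27.03, so φ = 0.16.
- ω_h reaches 0.50 when 49φ = 0.5(21.76 + 32.34φ), so φ = 10.88/32.83 = 0.33.

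The same algebra gives the range of φ in which alpha passes and ω_h is below 0.50:

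| Loading | Three factors (4/3/3) | Two factors (5/5) |
|---|---|---|
| 0.5 | none | none |
| 0.6 | 0.35 to 0.39 | 0.15 to 0.45 |
| 0.7 | 0.16 to 0.33 | 0 to 0.40 |
| 0.8 | 0.04 to 0.30 | 0 to 0.37 |

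**Extremes**
- Two uncorrelated five-item factors, L = 0.7: S = 10 + 40(0.49) = 29.6, alpha = 0.74, ω_h = 0. The rule passes a sum of two unrelated scores.
- One factor, L = 0.5: S = 10 + 90(0.25) = 32.5, alpha = 0.77 and ω_h = 25/32.5 = 0.77. There is no discrepancy.
- One factor at the retention floor, L = 0.4: S = 10 + 90(0.16) = 24.4, alpha = 0.66, which fails the rule.

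**The case against.** The strongest reply is that alpha is not the plan's test of dimensionality. That is the task of EFA with scree test and parallel analysis, then CFA in a separate subsample. Subscale alphas would stand beside the overall value, so a multi-factor result would be visible. This stands, and it limits the harm. It does not supply the missing condition: no stated step links the CFA result to how the overall alpha is read.

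A reader might infer that passing overall alpha is what licenses a total score. The article does not say so; it gives no scoring rule, and a total is only a plausible reading of its singular reference to the score. A reader might also infer that a total score will be compared across languages. The plan makes that comparison by multi-group CFA on the factor structure.

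The loadings and correlations are assumptions, and the window is limited: narrow for three factors at loading 0.6 and absent for ten items at loading 0.5. The three domains describe self-care, and self-efficacy is confidence across them, so one factor or strongly correlated factors are quite possible. All of this stands.

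Model-based remedies also have limits. With three first-order factors, a second-order model fits exactly as well as the correlated-factor model, so its fit is no extra test. With two, it is not identified without a constraint. A bifactor model with three or four items per group factor and about 100 patients per language group may be unstable.

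Finally, the Discussion sentence is a summary that goes on to mention reliability, and Methods assigns validity to other analyses. It is a slip to correct; it does not show that validity will rest on alpha.

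**Conclusion.** The concern holds in a limited form. The article fixes the coefficient, the threshold, its use on the overall scale and the favourable label, with no condition on dimensionality, so this is not a detail merely left to an analysis plan. At the plan's own expected length, the rule can call a total strongly consistent when a common factor explains 35% to 47% of its variance (4/3/3, loading 0.7, factor correlation 0.2 to 0.3).

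This is a possibility that rests on assumed loadings and correlations; it is not a forecast. It disappears with one factor. Across the ten-item layouts checked, the share below one half ends at factor correlations between about 0.30 and 0.45, and at 0.33 for the 4/3/3 layout with loading 0.7. Subscale alphas are unaffected. The documents do not support the stronger conclusion that the plan will adopt an unsupported total score, or compare one across languages, because alpha passed.

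**What to change.** 1. Keep alpha for each unidimensional subscale.
2. State that overall alpha will be read as support for a total score only if the planned CFA supports one factor.
3. If several factors are retained, report omega-hierarchical beside overall alpha, computed from the fitted correlated-factor or second-order model (with an equality constraint if there are two factors). State a minimum in advance. Below 0.50, less than half of the total's variance is common. With three factors this minimum has to carry the decision, since second-order fit adds no test.
4. If the minimum is not met, report and analyse subscale scores, including for the ROC cutoffs.
5. Delete *strong* at the 0.70 threshold and keep *acceptable*.
6. Correct the Discussion (Principal Findings) so that alpha is described as internal consistency in Phase 3, not as establishing internal validity.

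The cost is wording plus a small calculation from a CFA already planned in Mplus; no new data are needed. The downside is that a total score may turn out not to be supported.

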### Ethical Considerations

This research protocol has obtained ethics approval from the Ethical Committee of Ospedale San Raffaele (164/INT/2022) and will be conducted in accordance with the principles outlined in the Helsinki Declaration, Good Clinical Practice, and European law on the right to privacy (GDPR 679/2016). The confidentiality of all collected data will be strictly ensured during both data collection and analysis, with information analyzed in an aggregate manner to protect participants’ identities. Ethics approval will be obtained from each participating institute, with Istituto di Ricovero e Cura a Carattere Scientifico (IRCCS) Policlinico San Donato acting as the owner of the data.

Informed consent will be a mandatory requirement for every participant enrolled in the study, and health care professionals will be responsible for providing clear and detailed information about the study’s objectives to the participants. Participants will have the right to withdraw their informed consent at any point during the study without facing any repercussions or penalties. This research prioritizes the protection of participants’ rights, privacy, and well-being, adhering to ethical guidelines and ensuring that the study is conducted with the utmost integrity and respect for all individuals involved.

## Results

The forthcoming validation of the SCSE-OAC is poised to significantly advance our understanding of SE in managing OAC among patients with NVAF. Anticipated results are expected to affirm the scale’s robust validity features, including its construct, criterion, and content validity, affirming its reliability across diverse patient demographics. Through exploratory and confirmatory factor analyses, the SCSE-OAC is projected to exhibit a coherent factor structure that aligns with theoretical expectations, reinforcing its use as a psychometrically sound tool for assessing SCSE in OAC.

Subsequent analyses are anticipated to unveil significant correlations between SCSE scores derived from the SCSE-OAC and key clinical outcomes, such as medication adherence rates, incidence of bleeding or thromboembolic events, and overall patient quality of life. These findings will underscore the critical role of SE in the self-management of OAC, suggesting that higher SE levels are associated with improved health outcomes and adherence behaviors. Moreover, the study is expected to elucidate the relationship between SE scores and sociodemographic characteristics, including age, education, and health literacy, providing valuable insights into how these factors may influence patients’ confidence and capabilities in managing their treatment regimens.

The significance of this study extends beyond the validation of a novel measurement tool. It promises to contribute substantially to the field of patient-centered care in anticoagulation management by offering health care professionals a reliable means to assess and enhance SE among their patients [1]. The SCSE-OAC will enable targeted educational and supportive interventions designed to bolster self-management skills by identifying, for instance, patients at risk of poor adherence due to low SE; therefore, mitigating risks associated with suboptimal treatment adherence. Furthermore, the scale’s validation across different languages and cultural contexts is anticipated to facilitate its global applicability, paving the way for its adoption in varied clinical settings and among diverse patient populations.

## Discussion

### Principal Findings

This research protocol addresses a critical gap in OAC management by focusing on developing and validating SCSE for OAC treatment (SCSE-OAC). OAC is an internationally recommended treatment for patients with NVAF and plays a crucial role in preventing venous thromboembolism and stroke while requiring the adjustment of lifestyle to the chronic treatment that requires adherence [2,9,28]. However, low levels of adherence and persistence to OAC have been observed by previous research [29], leading to potentially preventable thromboembolic and hemorrhagic complications [30]. Understanding the determinants underlying patients’ adherence to OAC, particularly their SE, is of paramount importance to designing personalized patient-centered educational interventions. The SCSE-OAC, being a specific and theory-grounded tool, will aid in capturing patients’ confidence in performing self-care behaviors and provide insights into the challenges they face in OAC management. Consequently, the study’s findings will contribute significantly to enhancing treatment adherence, safety, and overall health outcomes for patients with NVAF.

The study aims to provide a comprehensive SCSE-OAC for English- and Italian-speaking populations through a multiphase and mixed methods research design. In the conceptualization phase, a systematic literature review will help identify challenges and issues in OAC self-care management. Subsequently, qualitative and quantitative methodologies involving patients and experts will refine the initial items’ pool. The validation phase will focus on establishing the internal validity of the SCSE-OAC using Cronbach α, ensuring the tool’s reliability and consistency. Additionally, a test-retest reliability study will assess the stability of the SCSE-OAC over time. Overall, the study is expected to yield a robust and culturally adapted SCSE-OAC that can be applied to evaluate patients’ SE levels in OAC management for each native-speaking group involved in the research.

While previous studies have examined determinants of OAC adherence [29], the SCSE-OAC represents a novel contribution to the field. The SCSE-OAC could provide a more focused and contextually relevant assessment of patients’ self-care behaviors in OAC management because it will adopt a specific theoretical framework and develop a theory-grounded measure of SE. Existing tools used to measure SE have been diverse and general, lacking specificity for the challenges specific to OAC treatment [10]. The SCSE-OAC’s development and validation will enhance the field’s understanding of SE’s role in OAC management and could contribute to the implementation of tailored patient-centered educational interventions, ultimately improving treatment outcomes.

### Limitations

Several limitations may be encountered during the course of this research. First, despite the efforts made to include a diverse sample of patients, there might be some variations in the characteristics of participants from different geographic regions, potentially impacting the generalizability of the findings. Additionally, self-reported data may be subject to recall bias or social desirability bias, potentially affecting the accuracy of the responses. Moreover, the reliance on patients’ self-assessment for some clinical variables, such as complications during OAC treatment, might introduce some subjectivity to the data. We also have to acknowledge that the study’s cross-sectional design limits the ability to establish causality between patients’ SE and specific health outcomes.

An additional limitation to note is the geographical scope of our study, which initially includes participants from Italy and Australia. The choice to focus on these 2 countries was primarily driven by logistical and feasibility considerations, including the availability of research networks and resources to support the study’s implementation. While this focus provides valuable insights into the SCSE of patients managing OAC in these regions, it may not fully capture English speakers’ linguistic and cultural nuances in Europe, such as those in Ireland or the United Kingdom. We acknowledge that the distinct differences in Australian English compared to UK English, along with varying health care systems and patient education practices, could influence the generalizability of our findings to other English-speaking populations. Therefore, we will extend the validation phase of our project to include researchers and participants from other countries who wish to contribute to this body of knowledge. Interested parties are encouraged to contact the authors for potential collaboration, allowing authors to evaluate and integrate scaling-ups of the project accordingly. This adaptive approach aims to enhance the SCSE-OAC’s applicability and relevance across broader linguistic and cultural contexts, addressing an acknowledged limitation of this study design.

